## Abstract

**Background:**

Good employee health and wellbeing is of key importance to employers and the economy. The workplace can serve as a setting for health and wellbeing promotion. Financial incentives may encourage employers to invest in employee health and wellbeing. The aim is to evaluate the effectiveness of health and wellbeing financial incentives offered to small medium enterprises in the West Midlands, UK.

**Methods:**

A cluster randomised controlled trial was designed to evaluate the effectiveness of a workplace health and wellbeing initiative with or without monetary incentives. We will evaluate the effectiveness of the financial incentive using a mixed methods evaluation approach.

**Discussion:**

The trial will help establish whether small-medium enterprises will improve their health and wellbeing offer and achieve higher employee awareness and participation in the offer in response to a monetary wellbeing incentive.

**Trial registration:**

AEARCTR-0003420, registration date: 17.10.2018, retrospectively registered.

**Electronic supplementary material:**

The online version of this article (10.1186/s12889-019-6582-y) contains supplementary material, which is available to authorized users.

## Background

Good employee health and wellbeing is of key importance to employers and the economy. For example in the workplace, 6.5 m employees reported musculoskeletal problems in 2008 and this is predicted to rise to 7 m employees by 2030 [1]. This equates to around 1 in 8 employees in England reporting having a musculoskeletal problem. In the West Midlands, the average number of sick days per person per year is 6.9. This indicates that up to 1.5 days per person per year could be lost due to MSK in the West Midlands. Similarly the impact of mental ill health in the West Midlands is significant; overall mental ill health costs the West Midlands an estimated £12.6 bn annually, equivalent to £3100 per population head, per year. Employment costs as a result of mental ill health represent 31.5% of this total at £3.9bn. These costs include absence and presenteeism, as well as the cost of worklessness [2].

As a setting for health promotion, workplaces enable access to large groups of people to promote health and wellbeing. The European Agency for Safety and Health at Work provides evidence that workplace health promotion can lead to cost savings for organisations by reducing staff turnover and sickness absence, and is a valuable complement to health and safety programmes [3]. The European Agency for Safety and Health at Work recommend that a range of options are provided to businesses to implement workplace health promotion. Despite this evidence, many businesses find it hard to invest in the health and wellbeing of their employees, or do not invest at all; problems that are especially true for small and medium size enterprises (SMEs). There has been considerable interest in the effect of financial incentives to stimulate change in the workplace environment, which have shown promising results in health care settings [4].

The increase in the last decade of schemes aimed at changing the health related behaviour of the public has been accompanied by evidence that even small incentives can positively influence choices [5–8]. Nationally there are two examples of using financial incentives to encourage employers to invest in employee wellbeing:Commissioning Quality and Innovation (CQUIN) [9] - initiative to improve health and wellbeing of NHS staff where employers are financially penalised if they do not achieve wellbeing targets. However, the fiscal incentive programme is designed to be a reward model rather than a penalisation model and reach a more diverse (and hard to reach) audience with significant barriers to uptake.Health, Work and Wellbeing Challenge Fund [10] - This was a Competitive grant scheme in 2010 for SMEs, coordinated by Department for Work and Pensions and informed by “Working for a healthier tomorrow” report [11], however given it was a Competitive grant process it appealed to SMEs already engaged in employee wellbeing with an understanding of its importance. The fiscal incentive programme was designed to reach the ‘unconverted’ SMEs. Furthermore outcomes for the funding were self-reported and no baseline measures were taken to compare results to.

Neither of the above examples has systematically measured the change in the employers’ perceptions at the organisation behaviour, health beliefs or health behavioural change.

This will be the first cluster randomised controlled trial (cRCT) of its kind to test a financial incentive in such a diverse range of organisational sizes and sectors. We intend to engage a mix of industries across the West Midlands economy currently giving the best chance of a nationally replicable programme. Furthermore a financial incentive has not been part of previous wellbeing commitments for employers so there is little to no comparable evidence about what changes an organisation has made and the effect on employees. Varying degrees of incentive has also not been previously been explored.

This study provides a unique opportunity to build the evidence for incentives to improve employee health and might help in identifying the financial ‘tipping point’ for employers to engage in improving the health and wellbeing of their employees. It will also build further understanding of the barriers and enablers for effective interventions aimed at employees. The intervention was designed and the research team was commissioned to carry out an independent evaluation, combining three interrelated aspects:Recruitment evaluation (to explore why some SMEs remained ‘unconverted’ and did not signed up to the trial)Impact evaluation (to systematically measure the change in the organisation behaviour) andProcess evaluation (to understand how changes take place or why they do not occur).

This work can inform national policy regarding the effectiveness (or otherwise) of financial incentives and discussions about wider roll-out.

The aim is to evaluate the effectiveness of wellbeing financial incentives to SMEs in the West Midlands, UK. This primarily is to establish whether SMEs will improve their health and wellbeing offer and achieve higher employee awareness and participation in response to a financial wellbeing incentive. The evaluation also aims to assess whether financial incentives help and motivate SMEs overcome barriers when aiming to improve their wellbeing of their employees.

## Methods

### Trial design

The evaluation will employ a mixed methods design of a four-arm cross-sectionally cRCT with baseline measurements. The trial will encompass two levels of the intervention and a modified Solomon method whereby two control groups are formed only one of which contributes base line measurements. The evaluation will comprise three elements: recruitment evaluation, impact evaluation and process evaluation.

### Study setting

The study will be carried out with SME’s located in the West Midlands region, UK.

#### Eligibility criteria

SMEs (10–250 employees) that are located in the West Midlands Combined Authority footprint; receptive to implementing health and wellbeing behavior changes within workplaces (with or without monetary incentives); willing and able to provide organizational level data; willing and able to allow employees time to complete questionnaires and to allow senior executives to be interviewed. Employee inclusion: employees who are 16 years of age or older; who hold an employment contract with the employer; and who are willing to provide written consent.

Any issues around right of withdrawal of employees will be addressed by implementing the following:Participants will be informed about their right to withdraw from the study at any time before the interviews commence.Participants will be made aware that they can stop the interview if they wish to withdraw from the study at any time.If participants decide to withdraw their data post interview, every effort will be made to remove their data, however this may not always be possible if analysis and publication has already taken place. They will be informed that they will not have to give a reason for withdrawing and this will not affect their circumstances in any way.If choosing to withdraw from the study, any data collected before withdrawal will be deleted and quotes will be removed from any written reports if it is possible to do so – as above, if publication has already taken place, this will not be possible (but this will be made clear to participants as part of the consent process).

### Interventions

The intervention is a monetary incentive that is designed to stimulate SMEs to improve the wellbeing offer to employees and promote the health of their workforce with respect to healthy behaviours such as mental health, healthy lifestyle and musculoskeletal health. The incentive will:Vary in size depending on the number of employees and will be given at two levels (i.e. a smaller (50%) and larger (100%) financial allocation) andIrrespective of the level, it would be paid in two instalments. The first instalment of 30% will be paid immediately following baseline assessments. The second instalment is based on how much of the Thrive at Work Bronze level Commitment has been implemented.

All SMEs (intervention and control) will receive a Thrive at Work Wellbeing Commitment Programme and Toolkit. This is a guideline that provides organisations with a structured method they can follow in order to improve the health and wellbeing of employees. Topics covered include mental health, musculoskeletal health, and healthy lifestyle. The Thrive at Work programme includes a supporting toolkit of available local and national resources that the company can draw on in their efforts to raise awareness of health issues among employees and to prompt employees to take action to improve their health and wellbeing. The Thrive at Work pack provides an opportunity for SMEs to attend quarterly network meetings that are designed to spread the best practice across SMEs in relation to the Thrive at Work Wellbeing Commitment Programme and Toolkit.

#### The toolkit in relation to the incentive

The toolkit is an inexpensive method than can be implemented at scale. The hypothesis that this study aims to test is that the uptake of toolkit can be increased by a monetary incentive.

### Outcome measures

The primary aim of the study is to establish whether SMEs will improve their health and wellbeing offer in response to a monetary wellbeing incentive targeted to the organisation not the individual. However, asking employers to assess themselves against this outcome is open to inaccurate self-assessment. Hence the need for an external assessment in which individual employees will be interviewed. The NHS Commissioning for Quality and Innovation (CQUIN) indicator specification [12] indicates the following question in the annual staff survey:

#### ‘Does your organisation take positive action on health and wellbeing?’

The sample size was calculated on the basis of this question.

### Additional outcomes

Additional outcomes will be collected from both employers and employees. Therefore, we will have two sets of results presented by status (employer vs employee). Questions will cover each of the key theme areas (i.e. lifestyle, musculoskeletal, mental health). Employee wellbeing will also be measured using the four main questions used by the Office for National Statistics to monitor national wellbeing [10]. See Additional file 1 for full questionnaire.

A number of the employee level questions will align with those asked to the employer in order to assess consistency between the two.

These questions cover the following:Awareness of information provided by the employer (directed to employer and employee)Likelihood of taking part in the health and wellbeing offer provided by the employer (directed to employer and employee)Improvement efforts carried by the employee (directed to the employee)Provision of activity / services provided by the employer (directed to employer and employee)Utilisation of activity/services by the employee (directed to employer and employee)

Additional measures for the employer will include:PoliciesRegulations

### Recruitment evaluation

The aim of the recruitment evaluation is to understand the reasons for non-participation in the trial thereby providing insight into the barriers, motivators and enablers that influence the success or otherwise of recruitment to the programme. SMEs in the West Midlands who had the opportunity to participate but did not do so will be approached to provide information on their reason for non-participation in order to inform future studies and policies, and so that any factors that may potentially affect drop out are considered in relation to the main study.

The recruitment evaluation questions are as follows:What (if any) aspects of the programme influenced organisations’ decision to participate or not participate?What (if any) aspects of the trial design influenced organisations’ decision to participate or not participate?What (if any) aspects of the recruitment process influenced organisations’ decision to participate or not participate?What other reasons (if any) influenced organisations’ decision to participate or not participate?

### Process evaluation

#### Intervention logic

A logic model (see Additional file 2) was developed in an internal workshop to capture the essential elements of the intervention and mechanisms through which the intervention is meant to work. The top level (in green) relates to the inputs to the trial provided by the intervention provider based on the Thrive at Work guidelines (website and toolkit) and provision of the financial incentive in SMEs in the intervention groups. The next level (in orange) relates to the activities that might be undertaken as a result of these inputs, for instance a health needs assessment being undertaken in response to the Thrive at Work toolkit. The next level (in red) relates to the outputs produced by these activities, such as employers’ increased knowledge and awareness as a result of additional support being put in place. The following layer (in blue) relates to outcomes i.e. more long-term changes taking place as a result of these outputs, for instance employees making healthier lifestyle choices. The final two layers relate to the goals (in turquoise) and long-term goals (in purple) of these changes. To give an example, one of the goals of the trial is to encourage a fitter, more resilient workforce, but this also feeds into a longer-term goal of reducing public spending on health and welfare.

The second model (see Additional file 3) focuses on the intervention in the form of the financial incentives and describes the theory behind the expected effects (outputs) of the intervention.

These models provide the basis for development of the main process evaluation questions briefly outlined below.

#### Process evaluation questions

We anticipate that the process evaluation, will cover eight high level topic areas. Within each area, we will design questions to identify the main mechanisms which drive behaviour change by employers and employees and the factors which act as motivators, barriers and enablers. As such, the process evaluation will complement the impact (quantitative) evaluation: it will examine how the incentive may interact with the Thrive at Work Commitment and toolkit and identify the mechanisms by which the incentive does or does not bring about change. The eight topic areas covered are shown below, with indicative examples of issues we propose to explore within each:Were the fiscal incentive, Thrive at Work Commitment and network meetings implemented with a high level of fidelity?How effective have communications about the intervention been (from West Midlands Combined Authority to employer and from employer to employee)?How have employers and employees identified what needs to change in terms of health and wellbeing activities and outcomes?What health and wellbeing offer was made by the employer before and since their participation in the trial?Have employees’ intentions or behaviour changed towards the health and wellbeing offer?To what extent (if at all) and how have the initial grant (and prospect of further payment) triggered commitment and activity on the part of the employer?To what extent and how have the Thrive at Work Commitment and toolkit been effective in facilitating behaviour change among employers and employees?How, if at all, have the network meetings helped employers enhance their health and wellbeing offer?

### Participant timeline

Baseline assessments will be collected from three arms (I^1^, I^2^, C^1^) but not one of the control arms (C^2^). Post-intervention quantitative assessment will be collected at 12 months from the four trial arms (I^1^, I^2^, C^1^, C^2^). The recruitment evaluation from clusters that decline will take place as soon as possible after recruitment closes and while memories of reasons for non-participation are still fresh. Process evaluation will collected throughout the trial period, in particular at post-randomisation (I^1^, I^2^, C^1^), midline (I^1^, I^2^) and post-intervention (I^1^, I^2^, C^1^, C^2^). Figure 1 illustrates trial and participant timelines.

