### Blinding (masking)

To avoid ascertainment bias, baseline bias assessments will be carried out prior to the start of the intervention so participants will not know which groups they have been randomised to when baseline assessment is carried out. SMEs will be informed of their random allocation post baseline assessments. This information will come from the West Midlands Combined Authority in a letter sent out via email after baseline assessment.

While randomisation provides strong protection against selection bias, we were concerned to avoid observer bias that could result if observers were aware of group allocations. To minimise this risk we decided to allocate separate observers, deployed from Warwick University, to conduct baseline vs. follow-up observations. Quantitative and qualitative data collection will be undertaken by Warwick University researchers (4 researchers) visiting the workplaces and interviewing employers and employees. Quantitative outcomes will be face-to-face with iPad tablets, whereas process evaluation will take place over the phone and/or face-to-face using a topic guide. Process evaluations follow quantitative evaluations so that the latter cannot contaminate the former. To minimise observer bias there are three methods proposed:Those who collect process data will not collect impact data from the same institution.Data collectors undertaking interviews with employees will not be informed of a companies’ allocated group.Outcomes data collectors will be asked of their suspicions about which group the SME they are collecting data from is in. This can then be compared to the actual groups the SMEs are in, to see how good the observer blinding has been. We will use a separate team of telephone interviewers in Cambridge (RAND) to conduct interviews with employers as part of the process evaluation (see below). These interviewers will not be blind to the allocation as they will ask questions about how the employers in the Intervention groups have used the money, and the value and impact of the network meetings. We will brief these interviewers not to share their knowledge with the team conducting interviews with employees for the process evaluation (who will thus remain blind to the allocation).

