#### Process evaluation

Process evaluation data will be collected using a combination of semi-structured interviews with employers and employees; document review (particularly of the Thrive at Work commitment and toolkit and other communication tools produced by West Midlands Combined Authority); direct observation and review of attendance records at the quarterly network meetings; and review of supporting evidence, such as the statements of spend produced by participating SMEs.

Detailed qualitative interviews will be undertaken in a sample of SMEs per trial arm (see Additional file 5). These will be selected to cover a spectrum in terms of size (with matched groups from each trial arm) and industry sector.

We will aim to interview - a minimum of 3 employees in the smallest SMEs, and a maximum of 6 in the largest (see Additional file 5), ideally with a different mix of individuals at each stage of the process evaluation. However, we will also be pragmatic about which employees we interview depending on availability on the day of our visit and in order to minimise disruption to the business activities of SMEs. The interviews will build on the logic model (see above) and focus on the barriers and facilitators of change at the organisational and individual level.

We want to interview SMEs from the control to understand what influences behaviour change among those employers receiving only the Thrive at Work commitment and toolkit and having the opportunity to attend network meetings. It will be instructive to see how the mechanisms of change and barriers for the control groups differ (if at all) from those observed in SMEs who do receive a financial incentive.

Separately, we will conduct telephone interviews with the Thrive at Work lead (i.e. official(s) sponsoring or overseeing participation in the trial) at each of these SMEs. These interviews will provide data on how the initial monetary incentive payment has been used by employers and what activities it has enabled, and on why employers chose to use it as they did. They will also enable us to understand: employers’ perceptions of the value and impact of the Thrive at Work commitment and toolkit; to what extent the final monetary incentive payment is motivating activity to achieve Thrive at Work accreditation; whether or not the employer has attended quarterly network meetings; and if so, what value these meetings had for them.

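### The midline process round is held only in the incentive arms before the 12-month outcome: the stated model cannot remove its effect (probably small), and employee process interviewers cannot then be blind to incentive versus control

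*Protocol article*

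**What the plan says.** **Timing.** The Participant timeline lists three process rounds: post-randomisation in I1, I2 and C1, then "midline (I^1^, I^2^) and post-intervention (I^1^, I^2^, C^1^, C^2". It also says: "Post-intervention quantitative assessment will be collected at 12 months from the four trial arms".

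**Who is interviewed.** Under Data collection, Process evaluation: "Detailed qualitative interviews will be undertaken in a sample of SMEs per trial arm". Each sampled SME contributes 3 employees (smallest) to 6 (largest), "ideally with a different mix of individuals at each stage of the process evaluation". The Thrive at Work lead is interviewed separately by telephone. The number of SMEs is in Additional file 5.

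**Blinding.** The Blinding section says: "Process evaluations follow quantitative evaluations so that the latter cannot contaminate the former". It accepts that the telephone interviewers of employers are unblinded, and tells them not to share what they know with "the team conducting interviews with employees for the process evaluation (who will thus remain blind to the allocation").

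**Model.** The Analysis plan has treatment effects, time effects, cluster and cluster-by-time random effects, and one term for whether the cluster had been measured earlier. No term covers process contact.

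**The concern.** The design treats measurement as a possible cause of change: it leaves one control arm unmeasured at baseline so that a measurement effect can be estimated. A midline round in the incentive arms alone adds a further contact that no control SME receives before the outcome.

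The process topics include what the employer now offers and whether employees' intentions or behaviour have changed. These lie close to the primary question, whether the organisation takes positive action on health and wellbeing. If the conversation shifts answers to that question, the shift is credited to the money.

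The same schedule also undermines a stated safeguard. If midline visits go only to incentive SMEs, the visit itself tells the interviewer that the SME is not a control.

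**Working it through.** The plan gives no figure for the effect of process contact. The nearest is the measurement effect simulated in the Sample size section, a relative risk of 0.9 to 1.1.

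**1. Can the model remove midline contact?** On the log scale, let a be the baseline level, t the time effect, m the prior-measurement effect, b1 and b2 the incentive effects, and d the average effect of midline contact. The expected follow-up levels are:

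| Arm | Follow-up level |
|---|---|
| C2 | a + t |
| C1 | a + t + m |
| I1 | a + t + m + b1 + d |
| I2 | a + t + m + b2 + d |

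C1 minus C2 gives m. I1 minus C1 gives b1 + d, and I2 minus C1 gives b2 + d. The stated fixed-effect design has 5 columns and rank 5. Adding a column for midline contact in every incentive SME gives 6 columns and still rank 5: the new column equals I1 + I2, with weight 0 on the prior-measurement term. If only some SMEs are visited, the rank is 6 of 6, so a separate term could be estimated, but the stated model has none.

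The post-randomisation round is different. It covers I1, I2 and C1, the arms that carry m, so the existing term largely absorbs it.

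**2. How large could the bias be?** Bias factor = 1 + s × e × (g − 1), where s is the share of incentive-arm SMEs visited, e the share of outcome respondents affected in those SMEs, and g the relative risk from contact.

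Inputs:
- 33 SMEs per arm, ten outcome interviews per SME and SME size 10 to 250 (protocol).
- s = 8/33 (assumption, because Additional file 5 is not shown).
- g = 1.1 (upper end of the protocol's own measurement range).

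Results:
- Only interviewed employees affected, 10-employee SME: e = 3/10, so 8/33 × 0.3 × 0.1 = 0.7%.
- Only interviewed employees affected, 250-employee SME: e = 6/250 = 0.024, so 8/33 × 0.024 × 0.1 = 0.06%.
- Whole SME affected: e = 1, so 8/33 × 0.1 = 2.4%.

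With g = 0.9 the sizes are the same and the signs reverse.

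**3. Range over the unknown share, whole SME affected (e = 1).**

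| Share s | Factor, g = 0.9 to 1.1 | True RR 1.3 becomes |
|---|---|---|
| 10% | 0.99 to 1.01 | 1.29 to 1.31 |
| 30% | 0.97 to 1.03 | 1.26 to 1.34 |
| 100% | 0.90 to 1.10 | 1.17 to 1.43 |

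The last row is only a bound, since the protocol says a sample of SMEs is interviewed.

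**4. Effect on the 95% posterior rule.** Take a true RR of 1, baseline 30%, ICC 0.06 (design effect 1 + 9 × 0.06 = 1.54), 33 versus 33 SMEs, g = 1.1, e = 1 and a normal approximation. The chance of meeting the rule is 5.0% with no contact, 6.6% at a 20% share and 7.5% at a 30% share.

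**5. Contrast between the two incentive levels.** If both arms have the same share and the same contact effect, the factor f cancels: (1.5 × f)/(1.3 × f) = 1.5/1.3.

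**6. Blinding.** Set the timeline beside the blinding text. At midline only I1 and I2 are visited. An employee interviewer who knows the schedule therefore knows that the SME is in an incentive arm, though not which one. A briefing that stops the telephone team from talking cannot prevent this.

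**The case against.** The strongest reply is that the effect is trivial and the text can largely be read consistently. Much of this stands.

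- **Sequencing.** A reader might infer that a midline round flatly contradicts the statement that process work follows quantitative work. That statement can be read wave by wave: baseline then post-randomisation interviews, 12-month assessment then post-intervention interviews. Midline has no quantitative wave to follow. The sentence is loose, and it does not cover the midline round, but a contradiction is not established.
- **Outcome assessors.** A reader might infer that those who collect the outcome are unblinded. The documents do not support this. "Those who collect process data will not collect impact data from the same institution"; outcome collectors are not told the allocation; and their guesses are recorded and compared with the truth. The same section also says "Quantitative and qualitative data collection will be undertaken by Warwick University researchers (4 researchers"), so leakage between colleagues is possible, but nothing shows it.
- **Extent.** One might count two pre-outcome rounds of 3 different people and say that 6 of 10 outcome respondents in an incentive SME have already been interviewed. That is the extreme for the smallest sampled SME, it treats a preference for different individuals as a certainty, and it includes the round that the model largely absorbs.
- **Direction.** Upward bias is plausible but unsupported: the protocol's own range is symmetric about 1.
- **Unseen files.** The number of SMEs (Additional file 5), Figure 1 and the full model (Additional file 6) are not shown. Employee interviews at midline follow from the reference to each stage of the process evaluation; the article does not list midline content explicitly.

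The reply does not remove the core: the contact is specific to the incentive arms, it precedes the outcome, the model as described has no term for it, and the blinding statement fails at midline.

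**Conclusion.** The point holds in a limited form. Midline contact in I1 and I2 cannot be separated from the incentive by the model as described, so any effect enters both incentive-versus-control estimates. Its likely size is small: 0.06% to 0.7% if only those interviewed are affected and 2.4% if the whole SME is, against design effects of 1.3 and 1.5. Its sign is unknown. These figures rest on an assumed 8 of 33 SMEs and an assumed 10% relative change. The comparison of the two incentive levels is unaffected if contact is equal in both arms.

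The statement that employee process interviewers remain blind to allocation cannot hold at midline for incentive versus control. The safeguards for outcome assessors are separate and are not contradicted. The change is worth making because the contact is avoidable and the remedy cheap, not because it threatens the main result.

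**What to change.** 1. **Sampling.** Where SME size allows, draw midline employee interviewees from outside the 12-month outcome sample. With ten outcome respondents and at least 3 interviewees, this needs at least 10 + 3 = 13 employees. In the smallest SMEs, where it is impossible, record who was interviewed. The outcome list must then be drawn before the midline visits.
2. **Sensitivity analysis.** Repeat the primary analysis without the process-visited SMEs in all four arms, or without the interviewed employees. Process SMEs are to be matched on size across arms, which helps to keep the first exclusion balanced. This is preferable to a covariate in the primary model: process SMEs are chosen purposively by size and sector, so its coefficient could mix contact with selection.
3. **Text.** Reconcile the Participant timeline with the Blinding section. State that midline process interviewers are not blind to incentive versus control, and that the rule that process work follows quantitative work does not apply to the midline round.

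**Cost.** The pool of midline interviewees is slightly narrower and there is one additional, less precise analysis: under the 8-of-33 assumption, excluding SMEs leaves 33 − 8 = 25 per arm. The primary model does not change.
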